### **2.3.3. EXPLORATORY OUTCOMES**

Not applicable.

### **2.3.4. ADDITIONAL ANALYSES**

It is likely that additional analyses will be carried out after the analyses specified in this SAP have been completed.

We shall investigate the use of Receiver Operator Characteristic (ROC) curve analyses, under the assumption that for subjects where neither test indicated surgery, both tests had accurately ruled out unilateral disease. We shall investigate alternative thresholds for continuous measures from AVS and 11C-Metomidate PET-CT. These analyses will be performed for all participants, and within subgroups defined by whether the alternative test was positive, negative, or ambiguous.

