#### C-metomidate scanning

Metomidate is a potent inhibitor of CYP11B1 (11 $\beta$ -hydroxylase) and CYP11B2 (aldosterone synthase). It is the methyl analogue of etomidate, an ethyl-imidazole anaesthetic agent which is used clinically in sub-hypnotic doses as an inhibitor of adrenal steroidogenesis in the management of refractory Cushing's syndrome.(18,19) Metomidate (itself used as a veterinary anaesthetic until the 1970's) can be CH3-labelled as a PET radiotracer (C-metomidate), and proof of concept of its high affinity binding to adrenal cortex was established *in vitro* and in primate studies as far back as 1998.(20) In the first human application, 15 patients underwent C-methionine imaging prior to surgery for a unilateral adrenal mass.(21) The nine histologically-diagnosed adrenocortical tumours each demonstrated high uptake and could be reliably discriminated from the six lesions which were not of cortical origin. In a larger follow up series, comprising 73 patients who underwent surgery for suspected adrenal lesions, the six histologically confirmed APAs demonstrated the highest C-metomidate uptake, with a standardised uptake value (SUV) of 30.7 compared to 18.4 in non-functional adenomas.(22) When combined with high-resolution CT scanning its sensitivity and precision both increase as the improved spatial resolution permits distinction of tumour from normal adrenal tissue (and separate measurement of SUV in each) with greater confidence.(23)

In a previous, non-randomised proof-of-concept study we showed that C-metomidate PET CT scanning is comparable to AVS in distinguishing unilateral from bilateral PHA.(24) In 35 patients with confirmed PHA and an anatomical adrenal abnormality, ROC analysis for PET-CT showed that the finding of >25% higher PET signal (SUVmax - maximum standardised uptake value) over an adenoma compared to the contralateral adrenal conferred 76% sensitivity and 87% specificity compared to AVS; specificity rose to 100% in patients whose absolute SUVmax over tumour was >17. Since then, considerable clinical experience with C-metomidate PET-CT scanning has been accumulated, although robust, randomized trial data are lacking to endorse its widespread use as the investigation of choice.(23,25).

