## **9.0 Follow-up management and investigations**

We anticipate ~50% of patients will be found on one or both investigations to have unilateral PA, and be recommended for adrenalectomy. The primary outcome measurements will be at 6 months after surgery.

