## **11.0 Diagnostic Investigations**

The primary control intervention is AVS and will be performed according to an identical protocol

at all centres whose internal audit data indicate a successful bilateral cannulation rate of >75%. Briefly, the femoral vein is cannulated under local anaesthesia and catheters advanced under fluoroscopic guidance into each adrenal vein.(17) The procedure is performed under conditions of ACTH stimulation, which facilitates unequivocal confirmation of secure adrenal vein cannulation. Blood samples from both adrenal veins and the lower part of the inferior vena cava are analysed for aldosterone (A) and cortisol (C) and an aldosterone/cortisol (A/C) ratio calculated at each site. Lateralisation (providing evidence for an adrenalectomy to be recommended) is deemed to exist if the A/C value in one adrenal vein is at least 4-fold higher than the other. In preparation for AVS, treatment to control blood pressure is limited to a non-dihydropyridine calcium antagonist (e.g. verapamil) and doxazosin (together with potassium supplementation as needed), as the treatments least likely to interfere with interpretation of aldosterone/renin measurements. Although some rise in blood pressure is permitted in preparation for AVS, severely hypertensive patients may require additional therapy according to clinical judgement.

The experimental intervention is  $^{11}\text{C}$ -metomidate PET-CT. There has been no change in the protocol used since the proof-of-concept study. Patients are treated with dexamethasone 0.5 mg 6-hourly for 3 days, then receive an injection of 250 mBq (on average) of  $^{11}\text{C}$ -metomidate, with CT and PET scanning of the adrenal area 20-30 minutes later. A positive (lateralization) result is indicated by a maximum standardised uptake at least 25% greater in one adrenal gland compared to the other.

The assessment of the two diagnostic modalities will be undertaken at a monthly MDT of endocrinologists and radiologists. Patients will be offered surgery if one or both techniques indicate unilateral disease. For the very small number of cases (we estimate 1 in 25 on the basis of the proof-of-concept study), where AVS and  $^{11}\text{C}$ -metomidate PET-CT each meet these criteria for lateralisation, but to opposite sides, we will defer to the Trial Steering Committee (TSC) (see section 11).

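### SAP 2.3.4 labels patients negative on both tests as free of unilateral disease because the tests said so, which fixes sensitivity at 100% at the operative cut-off in two planned ROC subgroups

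*Combined protocol and SAP*

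**What the plan says.** SAP 2.3.4 (Additional Analyses) states: "We shall investigate the use of Receiver Operator Characteristic (ROC) curve analyses", and does so "under the assumption that for subjects where neither test indicated surgery, both tests had accurately ruled out unilateral disease". It adds: "We shall investigate alternative thresholds for continuous measures from AVS and 11C-Metomidate PET-CT". The curves are planned for all participants and "within subgroups defined by whether the alternative test was positive, negative, or ambiguous".

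Protocol section 11.0 sets the route to an outcome: "Patients will be offered surgery if one or both techniques indicate unilateral disease". It also sets the PET-CT cut-off: "A positive (lateralization) result is indicated by a maximum standardised uptake at least 25% greater in one adrenal gland compared to the other". AVS lateralises at a four-fold difference in the aldosterone/cortisol ratio.

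The primary analysis (SAP 2.3.1) is confined to operated patients and judged on outcome after surgery. SAP 2.3.5 calls subgroup analyses done after the specified ones exploratory. The only sensitivity analysis listed (SAP 2.3.6) repeats the primary analyses without technical AVS failures.

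**The concern.** A patient negative on both tests is not offered surgery, so nothing later confirms or refutes the call. The SAP completes the label by taking the calls as correct. For these patients the reference standard is a function of the index tests.

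The effect is sharpest where the alternative test was negative or ambiguous. There, a patient is operated on only if the assessed test is positive, and everyone below its cut-off is labelled negative by rule. A false negative at that cut-off is impossible, and lowering the cut-off can never gain sensitivity. A search for alternative thresholds is therefore tilted, in those subgroups, towards the current or a stricter cut-off before any data are seen.

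The documents give reasons to doubt the assumption. Section 4.2 describes an equivocal AVS zone and causes of false-negative AVS. In section 4.1 the proof-of-concept PET criterion "conferred 76% sensitivity and 87% specificity compared to AVS". Cell A of the planning table (9 of the 44 points) is AVS unsuccessful with PET bilateral, and a failed AVS has not ruled anything out.

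At stake is whether the ROC output can be used to describe discrimination or to suggest new cut-offs.

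**Working it through.** **The plan's own figure.** No figure is stated for the ROC. The nearest, from the same table (protocol section 33.0, repeated in SAP 1.5), is the share of discordant patients in whom PET-CT is right: (D+H+I+O+Q)/(D+H+I+G+J+M+O+P+Q) = 20/25 = 80%. This reproduces, and the cells sum to 100%.

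**Inputs from the table (% of cohort).**
- Double-negative: A+B+E+F = 9+0+35+0 = 44.
- AVS bilateral: E+F+G+H = 45. PET-positive among them: (G+H)/45 = 10/45 = 22%. Unilateral among them, taking F=0 as true: 9/45 = 20%.
- PET unilateral overall: C+D+G+H+K+L+M+O+P+Q = 52.
- AVS unilateral: 35, of whom J+L+O+Q = 33 are cured and I+K+M+P = 2 are not.

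**Assumptions.** All test-positive patients are operated on; the SAP gives no label for those who are not. The noise score is independent of disease, with positive rate q, and it is the measure that makes the call. True unilateral prevalence in the subgroup is π.

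**Sensitivity, AVS-negative subgroup.** Labelled positives are PET-positive and cured, so none lies below the cut-off. Sensitivity there is 1 for every q and π. It falls only at stricter cut-offs: with q = 52%, calling the top 40% positive gives 0.40/0.52 = 77%.

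**AUC of pure noise, same subgroup.** Labelled positives lie in the top q. Labelled negatives are the share 1−q below the cut-off, which always rank lower, and the share q(1−π) above it, which rank lower half the time:

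AUC = [(1−q) + q(1−π)/2] / (1 − qπ)

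| q | Calculation at π = 0.20 | AUC | AUC for π = 0.05 to 0.50 |
|---|---|---|---|
| 22% | (0.778+0.089)/0.956 | 0.91 | 0.89–0.94 |
| 30% | (0.70+0.12)/0.94 | 0.87 | 0.86–0.91 |
| 50% | (0.50+0.20)/0.90 | 0.78 | 0.76–0.83 |
| 52% | (0.48+0.208)/0.896 | 0.77 | 0.75–0.82 |
| 70% | (0.30+0.28)/0.86 | 0.67 | 0.66–0.73 |

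With true labels for everyone the same score has an AUC of 0.50 and sensitivity q.

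**Simulation with N = 165** (AVS bilateral 45%, unsuccessful 20%, unilateral 35%; Mann-Whitney test, two-sided p<0.05 with AUC above 0.5).
- AVS-negative: significant in about 80%, 74% and 39% of trials at q = 30%, 50% and 70%.
- AVS-unsuccessful, taken as the ambiguous group with π = 0.5: AUC 0.83 at q = 52%, sensitivity 100%.
- All participants: AUC 0.57 at q = 22% and 0.60 at q = 52%. At q = 52%, sensitivity reads 63% against a true 52%.
- AVS-positive: AUC 0.50. All these patients are offered surgery whatever PET shows, so verification does not depend on PET and the artefact disappears.

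**Effect on PET sensitivity in all participants.** Let u be the share of double-negative patients who truly have unilateral disease (assumed; no document gives it). Cured patients are D+H+J+L+O+Q = 52. PET-positive and cured are D+H+L = 48, plus 0.25 for one of the two opposite-side cells O and Q. Sensitivity = 48.25/(52+44u):
- u = 0: 48.25/52 = 93%
- u = 5%: 48.25/54.2 = 89%
- u = 10%: 48.25/56.4 = 86%
- u = 20%: 48.25/60.8 = 79%

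Counting both O and Q as correct PET calls (48.5), as the sponsor's accuracy formula does, changes only the last, to 48.5/60.8 = 80%.

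**The case against.** The strongest reply is that this analysis is additional, the SAP says only that it will be investigated, and the assumption is stated openly. Surgical verification of double-negative patients is unavailable by design. All of that stands. A reader might infer that the trial's accuracy comparison is compromised; it is not, because SAP 2.3.1 uses operated patients and never uses this label. But disclosure does not remove the bias, and SAP 2.3.6 does not address it.

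Second, the sound subgroup (alternative test positive) is already planned. That also stands. It has few non-cured patients, and the SAP neither gives it priority nor warns about the other two.

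Third, 100% sensitivity is not general. It does not hold at stricter cut-offs, in AVS-positive patients or in the whole cohort. It also needs the ROC measure to be the one that decided the call, whereas SAP 2.2.3 and 2.3.2 list several PET measures and calls are assessed at the MDT. At q = 50%, a noise measure correlated 0.9 or 0.7 with the deciding one gives sensitivity of about 86% or 75% and AUC 0.75 or 0.69. The bias shrinks but remains.

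Fourth, the threshold tilt is confined to the negative and ambiguous subgroups. In all participants and in AVS-positive patients, cell J (3.5%) supplies verified PET-negative positives, so a lower PET cut-off can gain sensitivity.

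**Conclusion.** The concern holds for the additional ROC analysis and leaves the primary result untouched. In the alternative-test-negative and ambiguous subgroups, sensitivity at or below the operative cut-off is an identity for the measure that decided the call, so it says nothing about the test. For pure noise in AVS-negative patients the AUC is about 0.67 to 0.91, and it is significantly above 0.5 in about 39% to 80% of trials of 165. In all participants the inflation is modest, to about 0.57 to 0.60.

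The documents do not fix a single AUC. The range rests on an assumed positive rate of 70% down to 22%, a prevalence of 20% from the table, and surgery in all test-positive patients. A reader who pools failed with negative AVS would find significance in 99.7%, 99.2% and 82% of trials (q = 30%, 50%, 70%), but SAP 2.3.4 lists negative and ambiguous as separate subgroups, so those rates do not describe the AVS-negative one. The fall from 93% to 79% illustrates an assumed 0% to 20% range; it does not estimate the true error.

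**What to change.** Amend SAP 2.3.4 as follows.

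1. Make the already planned alternative-test-positive subgroup, in operated patients, the main ROC for each test: PET measures in AVS-positive patients, AVS measures in PET-positive patients. State that few non-cured patients are expected: 2% of 165 = 3.3 for the first (I+K+M+P) and 3.5% of 165 = 5.8 for the second (C+G+K+M+P), fewer if some are not operated on. Intervals will be wide.
2. Do not report sensitivity, AUC or thresholds from the alternative-test-negative or ambiguous subgroups as accuracy.
3. For the all-participants ROC, report sensitivity, AUC and best threshold over an assumed share of truly unilateral disease among double-negative patients, for example 0%, 5%, 10% and 20%.

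The cost is SAP wording and a few extra runs on data already collected. The downside is that the figures will be less precise and look less favourable.

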### **2.3.5. SUB-GROUP ANALYSES**

The study is not powered to detect subgroup effects. Any subgroup analyses that are performed after the analyses specified in this SAP have been completed will be exploratory only.

### **2.3.6. SENSITIVITY ANALYSES**

The primary analyses will be repeated after the exclusion of subjects for whom AVS was a technical failure.

## **2.4. SAFETY OUTCOMES**

### **2.4.1. SERIOUS ADVERSE EVENTS**

The characteristics of all serious adverse events (SAEs) recorded in the study will be summarised, including severity, relationship to study procedures, outcome, and duration. The number and percentage of participants experiencing at least one SAE will be reported as a whole and by MedDRA system organ class and preferred term. Summaries will be provided as a whole and in relation to whether the participant underwent surgery. For those who underwent surgery, summaries will be provided according to whether the onset date was prior to or after the date of surgery.

## **3. DATA CONVENTIONS**

Any data rules (e.g. handling of partial dates, missing data imputation) will be documented as part of the Statistical Analysis Validation Plan (SAVP) for the project, in a separate analysis dataset specification document.

## **4. DOCUMENT HISTORY**

This is version 1 of the SAP for MATCH, dated 22/02/2021, the initial creation.

## **5. TABLES**

A full list of data tables will be developed and agreed prior to the final analysis.

## **6. FIGURES**

No figures will be produced as part of the statistical outputs for this study, but may be generated in support of future manuscript preparation.

## **7. LISTINGS**

No formal data listings will be produced. The analysis datasets will be made available to the Chief Investigator after the final analysis.
